### Follow-up evaluation

The follow-up oral examinations will be conducted 6 months later in the kindergartens. The same examiner will perform the examinations using the same equipment, procedure, and diagnostic criteria as those used in the baseline examinations. Each child’s oral hygiene and caries status will be recorded. In addition, the presence of visible plaque and the statuses of the included carious surfaces will be assessed. The colour of the arrested caries lesion will be classified and recorded as well [15]. The dentist will also record any sign of a tooth’s non-vitality, such as tooth hypermobility and an abscess. The examiner will not serve as the operator for the fluoride application.

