### Objectives

The primary objective is to study the proportion of caries lesions arrested by topical 38% SDF therapy with increasing treatment application times. The secondary objective is to study staining effect (discolouration) of the caries lesion with increasing treatment application times of topical 38% SDF therapy.

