### Hypothesis

A monotonically increasing trend can be found between the SDF application time and the proportion of caries lesions arrested and intensity of discolouration of carious lesion.

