### Clinical examination

The trained dentist will perform clinical examinations of the participating children in the kindergartens. The dentist will carry out a careful visual inspection with the aid of a World Health Organization (WHO) Community Periodontal Index (CPI) periodontal probe and a front-surface dental mirror with light-emitting diode intra-oral illumination [11]. The oral hygiene status will be measured using the visible plaque index (VPI). Both the buccal and the lingual surfaces of six index teeth (55, 51, 63, 71, 75, and 83) will be examined [12]. The presence or absence of visible plaque on the caries surface will also be recorded.

Tooth status (decayed, missing, filled surface [dmfs] score), tooth discolouration, and hyper-mobility will be recorded in the chart [13]. Teeth with carious lesions extending into the pulps, or signs suggesting that the teeth are non-vital, such as tooth discolouration, hypermobility, or abscesses, will not be included in this study. Dental caries will be diagnosed at the cavitation level. The carious lesion will be gently explored using a WHO CPI probe in the centre of the lesion [14]. Great care will be taken to avoid tooth damage during the probing. A carious lesion will be recorded as active if softness is detected, whereas if the dentine surface is hard to probe, it will be classified as an arrested caries [6, 12]. All surfaces (i.e., buccal, lingual, mesial, distal, and occlusal for the posterior teeth) of each tooth will be assessed. In addition, the colour of the carious lesion will be classified into one of four categories according to PANTONE colour plates (Table 2) placed next to the carious lesion [15]. The primary endpoint or outcome measure is active carious lesion at baseline that becomes arrested in the 6-month follow-up. The same dentist will serve as the examiner throughout the 6-month follow-up. Intra-examiner agreement on the plaque and caries assessment will be monitored and conducted in 10% of the children at each stage of the clinical trial.

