### Interventions

An independent operator will use a micro-brush (Advantage Arrest Applicators, Regular size, Elevate Oral Care, FL, US) to apply the 38% SDF solution. Each carious lesion will receive a single application of 38% SDF at different application times according to the allocated group. The amount of 38% SDF solution to be applied is approximately 0.004 mL [17]. The children will be instructed not to eat or drink for an hour after the SDF application. The carious surfaces will become hard and black if the treatment has successfully arrested the carious lesions. In case any harm occurs, the principal investigator will monitor the child and report the incident to the institutional review board (IRB). After the baseline examination, the research assistant will provide a report on the child’s oral health status to the parents. The report will feature a note asking the parents to report to the dentist if they notice any side effects on the treated tooth and the surrounding gingival tissue after SDF treatment.

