### Sample size and power calculation

The sample size is estimated based on a caries arrest rate of 70% [19] for a 60s application. We assume that a monotonically increasing trend exists and that the caries arrest rate is 80% for a 180 s application. Therefore, the expected caries arrest rates are 65.25%, 65.42%, 65.83%, 66.25%, 67.50%, 68.75%, 70.00%, 75.00%, and 80.00% for 3-s, 5-s, 10-s, 15-s, 30-s, 45-s, 60-s, 120-s, and 180-s applications, respectively. The power will be set at 90%, and the one-sided type I error (α) will be set at 0.025 (equivalent to a two-sided type I error of α = 0.05). The required sample size for detecting proportion trends is 104 surfaces of carious lesions per group [20]. In this study, the mean number of surfaces of carious lesions at baseline per child is estimated to be 4.75 [14]. In addition, the anticipated intraclass correlation coefficient is 0.23. This clinical trial requires 195 surfaces of carious lesions from 41 children per group following the equation for a multi-level study [21]. We assume that the dropout rate is 0.5% and the non-compliance rate is 10%. At least 46 children per group, or a total of 414 children at baseline, need to be recruited for this randomised clinical trial.

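### The follow-up section records 6-month colour for arrested lesions, while the staining objective concerns all carious lesions; the sections need reconciling so that active lesions are not left without a colour

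*Protocol article*

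**What the plan says.** The staining question is set in the Objectives section of the protocol article: "The secondary objective is to study staining effect (discolouration) of the caries lesion with increasing treatment application times of topical 38% SDF therapy". The Hypothesis section pairs it with the primary outcome and expects a monotone rise with application time in "the proportion of caries lesions arrested and intensity of discolouration of carious lesion". Neither statement is limited to lesions that arrest.

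On measurement, the Clinical examination section says that "the colour of the carious lesion will be classified into one of four categories according to PANTONE colour plates", again without restriction. The caption of Table 2 likewise refers to dentine carious lesions in general.

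The Follow-up evaluation section makes two statements that bear on the 6-month visit. The first is general: "The same examiner will perform the examinations using the same equipment, procedure, and diagnostic criteria as those used in the baseline examinations". The second is specific to colour: "The colour of the arrested caries lesion will be classified and recorded as well". It is the only sentence in the article that names which lesions have their colour recorded at 6 months. Between the two, the same section has the status of all included carious surfaces assessed, so it uses a wider term for status than for colour.

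The Interventions section links colour to arrest: "The carious surfaces will become hard and black if the treatment has successfully arrested the carious lesions". The Statistical methods section names no analysis set or method for colour.

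**The concern.** Arrest at 6 months is the primary outcome. It is observed after randomisation, and the trial is built on the expectation that it rises with application time. If colour is recorded only where a lesion has arrested, the lesions with a colour are a different selection in each arm. A comparison of colour among them is no longer a comparison of the randomised groups. It asks how dark lesions are given that they arrested, whereas the stated objective asks how dark treated lesions become as application time increases.

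This concerns data collection, so a later analysis plan cannot repair it. There is one follow-up visit, and a colour not recorded then is lost. At stake is the only secondary objective the article states.

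**Working it through.** **1. The sections side by side.**

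| Section | Lesions whose colour is meant |
|---|---|
| Objectives | the caries lesion, unrestricted |
| Hypothesis | the carious lesion, unrestricted |
| Clinical examination | the carious lesion, unrestricted, four categories |
| Follow-up evaluation, general sentence | as at baseline, hence unrestricted by implication |
| Follow-up evaluation, colour sentence | the arrested lesion |

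Four entries point one way. The one that is explicit about colour at 6 months points the other.

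**2. The plan's own figures, reproduced.** The planning arrest rates are given as "the expected caries arrest rates are 65.25%, 65.42%, 65.83%, 66.25%, 67.50%, 68.75%, 70.00%, 75.00%, and 80.00" per cent for 3, 5, 10, 15, 30, 45, 60, 120 and 180 s. They follow 65 + 5 × (seconds/60). A Cochran-Armitage calculation with seconds as scores, one-sided α 0.025 and power 90% gives 103.41, rounded up to 104 surfaces per group. The design effect is 1 + (4.75 − 1) × 0.23 = 1.8625. Then 104 × 1.8625 = 193.7 surfaces, and 193.7/4.75 = 40.8, so 41 children, or 41 × 4.75 = 194.75, about 195 surfaces. Finally 41/(0.995 × 0.90) = 45.8, so 46 children per group and 46 × 9 = 414. All stated figures reproduce, and 195 surfaces per arm is used below.

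**3. Lesions without a colour under the literal reading.** The share is 1 − arrest rate.
- 3 s: 1 − 0.6525 = 34.75%; 195 × 0.3475 = 67.8, about 68 surfaces.
- 180 s: 1 − 0.80 = 20%; 195 × 0.20 = 39 surfaces.
- All arms: the nine rates sum to 624.00%, a mean of 69.33%. The missing share is 30.67%, and 9 × 195 = 1,755 surfaces × 0.3067 gives about 538.

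So the missing share would fall by 34.75 − 20 = 14.75 percentage points across the range of application times.

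**4. What selection could do (assumed colour rates; the article gives none).**

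*(a) A difference in all lesions that is absent among arrested ones.* Suppose 90% of arrested lesions are dark in every arm, and a share q of active lesions is dark. The all-lesion rate is (arrest rate × 0.90) + (1 − arrest rate) × q. The 180 s minus 3 s difference is therefore 0.1475 × (0.90 − q):
- q = 10%: 74.0% − 62.2% = 11.8 points
- q = 30%: 78.0% − 69.15% = 8.85 points
- q = 50%: 82.0% − 76.1% = 5.9 points

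The arrested-only difference is 0 in each case.

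*(b) A difference among arrested lesions that application time did not cause in any one lesion.* Suppose lesions that arrest at 3 s would also arrest at 180 s and are 90% dark at either time, and the further 14.75% that arrest only at 180 s are dark in a share m. The arrested-only rate at 180 s is (0.6525 × 0.90 + 0.1475 × m)/0.80, against 90% at 3 s:
- m = 30%: 78.9%, difference −11.1 points
- m = 50%: 82.6%, difference −7.4 points
- m = 70%: 86.3%, difference −3.7 points
- m = 90%: 90.0%, difference 0

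The two cases show that the distortion can take different forms. They do not estimate it.

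**The case against.** The strongest reply is that the colour sentence is loose wording, not a restriction. It does not say that only arrested lesions are coloured. The general sentence in the same section repeats the baseline procedure, and that procedure classifies the colour of carious lesions without limit. The Clinical examination section is not confined to baseline either: it also defines the 6-month endpoint and covers agreement checks at every stage. On this reading every lesion gets a colour and nothing is lost. This stands to the extent that the loss is conditional on the literal reading. It does not remove the discrepancy, because a specific sentence follows a general one, and a follow-up form drafted from the specific sentence would omit active lesions.

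A second reply is that no staining analysis is written, and the choice of analysis set may properly sit in a statistical analysis plan that is not shown. That is right, and the missing analysis set is not held against the article. What is recorded at the visit is a separate matter, and on that the article speaks and is inconsistent.

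A third reply concerns the illustrations. Case (a) lets application time act on colour only through arrest, so its differences are the 14.75-point arrest difference rescaled; they do not show a separate staining effect being lost. That is correct, and it is one reason why neither case is offered as an estimate.

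**Conclusion.** The article is inconsistent about which lesions have their colour recorded at 6 months, and the sections must be reconciled. If the follow-up sentence is taken literally, 34.75% of lesions at 3 s, 20% at 180 s and about 31% overall would have no 6-month colour, and any staining comparison would rest on a set selected by an outcome expected to differ by arm. These shares assume the planning arrest rates hold.

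Three stronger conclusions might be inferred, and the article supports none of them:
- That the trial has chosen to analyse staining within arrested lesions. No staining analysis is specified.
- That restricting to arrested lesions removes most of the variation in colour. This would rest on the single remark that arrested surfaces turn hard and black, yet the plan grades arrested lesions for colour and provides four categories.
- That a staining effect of a known size, for instance about 10 points, would be hidden. Any such figure needs colour rates that the article does not give. Neither the size nor the direction of the bias can be computed.

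The point bears on the secondary objective only. The primary endpoint, its trend test and the sample size of 414 are unchanged. It should be fixed, but it is not critical to the trial's main result.

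**What to change.** In the Follow-up evaluation section, replace the colour sentence with one to this effect: *the colour of every treated lesion, whether active or arrested at 6 months, will be classified and recorded*. Make the follow-up form match. State that colour will be compared by assigned application time in all randomised treated lesions, with allowance for clustering within child, and that colour among arrested lesions will be reported as descriptive only.

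The cost is slightly more recording time at the visit. The examiner already assesses the status of each included surface, and the baseline equipment, which includes the colour plates, is to be used again. No change to sample size is needed. The change has to be in place before the 6-month examinations, since missing colours cannot be recovered afterwards.

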### Data management and access to data

The statistician and co-investigators will work closely with the principal investigator to monitor trial conduct and safety, assess risks and benefits, and make recommendations to protect the participants of this clinical trial. Two independent research assistants will enter and compare the collected data to minimise data entry errors. The statistician will oversee the data entry, checking, and analysis. The investigators, the research assistant and the statistician have access to the data.

### Auditing

An independent auditor will conduct a systematic and independent examination of the trial-related activities and documents. The auditor will check the informed consent forms, documentation of the consent process and reported data to ensure protocol compliance.

### Protocol amendments

The principal investigators will report any amendment of the trial protocol or changes of the eligibility criteria, outcomes or analyses to the local institutional review board and to the trial registry.

### Outcome measure

The outcome measure (primary endpoint) is the carious lesion’s activity (active/arrested) at the tooth-surface level at 6 months post initial treatment. The outcome measure will be administered at baseline and at the 6-month follow-up examination. The children and their parents have the right to receive dental treatment from other dentists. Based on our knowledge and experience in the previous clinical trials [13, 14, 18], other dental personnel generally will not care for the participating children, and we will include questions about the receipt of other dental treatments at baseline and during the follow-up interviews.

### Post-trial care

All children will be under care through the outreach kindergarten service. Children who experience any side effects from the SDF application will be followed up by the outreach dentist.

### Sample size and power calculation

The sample size is estimated based on a caries arrest rate of 70% [19] for a 60s application. We assume that a monotonically increasing trend exists and that the caries arrest rate is 80% for a 180 s application. Therefore, the expected caries arrest rates are 65.25%, 65.42%, 65.83%, 66.25%, 67.50%, 68.75%, 70.00%, 75.00%, and 80.00% for 3-s, 5-s, 10-s, 15-s, 30-s, 45-s, 60-s, 120-s, and 180-s applications, respectively. The power will be set at 90%, and the one-sided type I error (α) will be set at 0.025 (equivalent to a two-sided type I error of α = 0.05). The required sample size for detecting proportion trends is 104 surfaces of carious lesions per group [20]. In this study, the mean number of surfaces of carious lesions at baseline per child is estimated to be 4.75 [14]. In addition, the anticipated intraclass correlation coefficient is 0.23. This clinical trial requires 195 surfaces of carious lesions from 41 children per group following the equation for a multi-level study [21]. We assume that the dropout rate is 0.5% and the non-compliance rate is 10%. At least 46 children per group, or a total of 414 children at baseline, need to be recruited for this randomised clinical trial.

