### Randomisation and treatment allocation

The participating children with caries will first be categorised as either (1) having a high caries rate (or severe early childhood caries as defined by the American Academy of Paediatric Dentistry, 2008), which is defined as the presence of more than three untreated caries surfaces, or (2) having a low caries rate [16]. The children will be allocated via a stratified randomisation method with a block size of 18 into nine groups for the application of 38% SDF (Advantage Arrest Silver Diamine Fluoride 38%, Elevate Oral Care, FL, USA) on each carious lesion (Fig. 2):

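### The clustering adjustment treats surfaces per child as constant at the mean of 4.75; with varying counts, power at 41 analysable children per group is below the stated 90%

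*Protocol article*

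**What the plan says.** All planning figures are in the protocol article, Sample size and power calculation. On power and error rate: "The power will be set at 90" per cent, and "the one-sided type I error (α) will be set at 0.025 (equivalent to a two-sided type I error of α = 0.05". On effect: "the expected caries arrest rates are 65.25%, 65.42%, 65.83%, 66.25%, 67.50%, 68.75%, 70.00%, 75.00%, and 80.00" per cent across the nine application times. Before clustering: "The required sample size for detecting proportion trends is 104 surfaces of carious lesions per group". For clustering there are two inputs, "the mean number of surfaces of carious lesions at baseline per child is estimated to be 4.75" and "the anticipated intraclass correlation coefficient is 0.23". The result is "This clinical trial requires 195 surfaces of carious lesions from 41 children per group following the equation for a multi-level study". An allowance of 0.5% for dropout and 10% for non-compliance then takes this to 46 children per group and 414 in total.

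No standard deviation or CV of surfaces per child is given. Under Randomisation and treatment allocation, children are divided into a low and a high caries stratum, the latter being one "which is defined as the presence of more than three untreated caries surfaces".

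The endpoint is lesion activity at tooth-surface level (Outcome measure). The test is a Cochran-Armitage trend test corrected for clustering (Statistical methods). The article does not name the correction or say how children with different numbers of lesions are weighted.

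**The concern.** When lesions are nested in children, the variance of a pooled lesion proportion depends on how unevenly lesions are spread as well as on the mean number per child. A child with twelve lesions adds far more shared variance than two children with six. A formula that uses only the mean gives the smallest possible design effect for that mean and intraclass correlation, so it is optimistic whenever counts differ.

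At stake is the stated 90% power. Statistical methods and the Discussion both present that level as protection against a plateau in arrest before 180 s. Variation in surfaces per child uses up part of the same cushion, so the protection is thinner than it appears.

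**Working it through.** **Step 1. Reproduce the 104.** Use seconds as scores (mean 52), the nine listed rates, one-sided α 0.025 and power 0.90.

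- Σ(d − 52)² = 29,348 and Σp(d − 52) = 24.4565.
- Mean rate p̄ = 0.6933.
- Null variance term: p̄(1 − p̄) × 29,348 = 6,240.0.
- Alternative variance term: Σp(1 − p)(d − 52)² = 5,365.6.
- n = (1.960 × √6,240.0 + 1.2816 × √5,365.6)² / 24.4565² = (154.83 + 93.87)² / 598.12 = 103.4, rounded up to 104.

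**Step 2. Reproduce 195, 41, 46 and 414.**

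- Equal-cluster design effect: 1 + (4.75 − 1) × 0.23 = 1.8625.
- 104 × 1.8625 = 193.7 surfaces.
- 193.7 / 4.75 = 40.8, so 41 children.
- 41 × 4.75 = 194.75, so 195 surfaces.
- 41 / (0.995 × 0.90) = 45.8, so 46 per group; 46 × 9 = 414.

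Every printed figure comes out, so the equal-cluster form is what was used.

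**Step 3. How much variation do 41 children allow?** For a pooled lesion proportion with mᵢ surfaces in child i, the design effect is Σmᵢ[1 + (mᵢ − 1)ρ] / Σmᵢ = 1 + [(1 + CV²) × 4.75 − 1] × 0.23. With 41 children the largest affordable design effect is 194.75 / 104 = 1.8726. That gives CV² = (1.8726 − 1.8625) / (4.75 × 0.23) = 0.0092, or CV about 0.10. Counts that tight would mean almost every child having four or five surfaces (75% at five and 25% at four gives CV 0.09). The low stratum would then be empty.

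A mild case that fills both strata: half the children at three surfaces and half at 6.5 on average, with no variation inside either stratum. The CV is 1.75 / 4.75 = 0.37. Other assumed shapes with mean 4.75 give 0.41 (one plus Poisson) and 0.89 (one plus geometric).

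**Step 4. Power with 41 analysable children per group, lesions counted equally.** Effective n = 194.75 / design effect, and power = Φ[(24.4565 × √n − 154.83) / 73.25], where 73.25 = √5,365.6. All CVs are assumptions.

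| CV | Design effect | Effective n | Power |
|---|---|---|---|
| 0 | 1.86 | 104.6 | 90.3% |
| 0.37 | 2.01 | 96.8 | 87.9% |
| 0.4 | 2.04 | 95.6 | 87.5% |
| 0.5 | 2.14 | 91.2 | 85.9% |
| 0.6 | 2.26 | 86.3 | 83.9% |
| 0.8 | 2.56 | 76.0 | 78.7% |
| 1.0 | 2.96 | 65.9 | 72.5% |

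**Step 5. The same with efficient weighting.** If each child contributes information m / [1 + (m − 1) × 0.23], effective n is 41 times its mean. With one plus negative-binomial counts of mean 4.75, effective n is 98.3, 96.0, 91.3 and 86.6 at CV 0.5, 0.6, 0.8 and 1.0. Power is 88.4%, 87.7%, 85.9% and 84.0%.

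**Step 6. The margin from 41 to 46.** If all 46 were analysed with no dilution of effect, lesion-weighted power would be 91.1% at CV 0.4, 89.7% at 0.5, 88.0% at 0.6, 83.4% at 0.8 and 77.6% at 1.0.

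**The case against.** The strongest reply has four parts.

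*Nothing is miscalculated.* Correct. Each figure follows from its inputs, and a mean cluster size is a common planning simplification. A reader might infer that the article claims exactly 4.75 surfaces for every child, or that it stratifies because counts vary. It says neither: 4.75 is called a mean, and no reason for stratifying is given. Constant size is implied by the formula that reproduces the figures; the cited source of the equation is not at hand. The stratum boundary shows only that counts are expected to fall on both sides of it.

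*The weighting is not specified.* This also stands. The article names no clustering correction, and it mentions a separate statistical analysis protocol that is not shown and may settle the matter. The 72.5% to 87.5% range therefore cannot be read as the power of the planned test; it applies if lesions are pooled without weighting. Step 5 gives the smaller loss under efficient weighting.

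*The CV is unknown.* True, and it limits the claim about size. It does not affect direction: any CV above zero raises the pooled design effect, and one above about 0.10 exceeds what 41 children can carry.

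*Recruiting 46 covers it.* Only partly. At CV 0.4 it would, if nobody dropped out and non-compliance diluted nothing. But the article has already assigned that margin to dropout and non-compliance. Under its intention-to-treat analysis non-compliant children stay in their allocated group and can flatten the trend. The margin cannot be counted twice.

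**Conclusion.** The point holds as a planning assumption that the design contradicts. The design effect of 1.8625 needs near-constant surfaces per child, and stratification at more than three surfaces rules that out in practice. Power with 41 analysable children per group is therefore below the stated 90%.

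The size depends on two things that the article does not fix, the CV and the weighting. For assumed CVs of 0.4 to 1.0, lesion-weighted power is about 87.5% down to 72.5%. With efficient weighting and shifted negative-binomial counts it is about 88% at CV 0.5 to 0.6 and 84% at CV 1.0. Both ranges take the intraclass correlation of 0.23 and the linear rise in arrest rates as given.

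A reader might go further and conclude that the trial is too small, or that pooling lesions is the wrong analysis. The document supports neither. At a modest CV the loss is a few percentage points, and pooling lesions is the direct estimate of the proportion of lesions arrested, which is the stated aim.

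**What to change.** Take the CV (or standard deviation) of carious surfaces per child from the prior trial that supplied 4.75, or from this trial's baseline data. Replace 1.8625 with 1 + [(1 + CV²) × 4.75 − 1] × 0.23 if lesions are counted equally, or with the matching expression if the clustering correction weights children. Name the correction and restate the power for it. If the CV cannot be obtained, state that equal cluster sizes were assumed and show power over a range of CVs.

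A model with exchangeable within-child correlation may be considered as a sensitivity analysis, specified before outcome data are seen. It should carry a note that it gives less weight to each lesion in children with many lesions. If arrest varies with caries burden, it may target a different proportion from the lesion-level one in the aim.

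The number of children does not change, and nothing clinical is affected. The cost is one recalculation, a sentence or two of text, and a stated power that becomes less favourable.
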